|  |
| ***3. The objective(s) and endpoint(s), if different from the objective(s)*** |
| - To evaluate the effects of low-dose pioglitazone (7.5 mg/day) on glucose metabolism compared with a standard-dose of pioglitazone (15.0 mg/day) among Thai patients with T2DM with CKD. - To determine side effects related to weight gain and fluid retention and the incidence of edema of low-dose pioglitazone (7.5 mg/day) compared with a standard-dose of pioglitazone (15.0 mg/day) among Thai patients with T2DM with CKD. |
|  |
| ***4. The study design*** |
| **A randomized, open-label controlled clinical trial.**  **Method**   1. The study will be started after the institute review board approval, Royal Army Medical Department. 2. Electronic case record form will be designed with subject code that personal subject’s data is not identified. 3. Patient screening will be conducted according to inclusion criteria and exclusion criteria. 4. Subjects will be divided into 2 groups (low and standard dose pioglitazone) by block randomization. The randomization and drug dispensing will be done by the investigator. The inform consent form will be read by the research staffs to the subjects and will be signed by every participated subjects. 5. The intervention group will receive pioglitazone 7.5 mg, 1 tablet 30 minutes before meal, once a day in the morning and the control group will receive the pioglitazone 15 mg as prior to the study. A recommendation card with detail of side effect and drug interaction will be provided to each subject who receives pioglitazone. 6. Five mL of blood will be collected along with 2 urine containers (at least 2 mL of urine per container) prior to the first treatment for the following items: CBC, fasting blood glucose, serum albumin, HbA1C, lipid profiles, BUN, creatinine, electrolyte, and liver function test. Body composition was assessed immediately after dialysis. Dual energy x-ray absorptiometry (DEXA) scan will be used to measure lean body mass and fat mass in grams using a whole-body scan. 7. At week 4, 8, 12, 16, 20, 24 visit, the investigator does the physical examination, symptom and drug adverse event interview, and laboratory testing such as CBC, fasting blood glucose, serum albumin, HbA1C, lipid profiles, BUN, creatinine, electrolyte, and liver function test. DEXA scan will be repeated. Contact can be made to the investigator for 24 hours regarding to any abnormal event occurs. |
|  |

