| **Expected number of subjects: 74 subjects**  **Inclusion criteria**   1. Age 18 years or older 2. Diagnosed T2DM with stable glycemic treatment with HbA1c>8% at least 12 weeks and diagnosed CKD according to [Kidney Disease: Improving Global Outcomes](https://www.google.co.th/url?sa=t&rct=j&q=&esrc=s&source=web&cd=8&cad=rja&uact=8&ved=0ahUKEwid7tCq8rPLAhVDBY4KHaXbAs8QFggyMAc&url=https%3A%2F%2Fwww.guideline.gov%2Fbrowse%2Fby-organization.aspx%3Forgid%3D2349&usg=AFQjCNFB0TRXT4TlgKTcrEguhdpN6NSZxg) (KDIGO) 2012 definition 3. No history of treatment with TZDs within 12 weeks before starting the study 4. Normal liver function, which referred to AST less than 105 U/L and ALT less than 120 U/L 5. Subject with signed consent form.   **Exclusion criteria**   1. Active malignancy 2. Severe heart, lung or liver disease, stroke, chronic infection, e.g., tuberculosis within one year of starting the study 3. Limited life expectancy within 12 months, edematous state from any cause 4. Specific contra-indications to pioglitazone including increased serum levels of liver enzyme (aspartate aminotransferase [AST] or alanine aminotransferase [ALT] >2.5 times the upper limit of normal), and history of bladder malignancy. 5. Subject without signed consent form   **Withdrawal or termination criteria**   1. The occurrence of heart failure or volume overload after drug administration which resulted in treatment needed or consent form withdrawal. 2. The occurrence of side effect which resulted in consent form withdrawal such as dizziness that affect driving, diarrhea that affect routine life. 3. The occurrence of severe infection, cardiac arrhythmia, myocardial infarction and cardiovascular hospitalization.   **Subject allocation**  Block randomization divides subjects into low dose group and standard dose group equally. A randomization in each group is conducted by dividing each subgroup into 20 groups with the setting number 0-19. The even number group, classified as A, is the intervention group. And the odd number group, classified as B, is the control group. |
|  |
| ***11. Key study assessments and procedures*** |

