| The sample size was determined by using change in body fluid as the primary outcome measure and by extrapolating expected changes and standard deviation from data in the study of the effect of pioglitazone in T2DM patients. The target sample size was 37 subjects per group that will provide 80% power to detect a significant effect, using a 2-sided, *p*=0.05. **Formula:**  **Value description**  ** = 0.05 (two-tail)  = 1.96**  ** = 0.20  = 0.84**  **[figure not shown]**  **n = **  **[figure not shown]**  By the calculation, the quantity of subject per group is 37. But with the follow up, the 10% loss follow up of the calculated number is considered. Therefore, the quantity of subject per group is 40, total is 80.  Statistical analyses were performed using the Statistical Package for Social Sciences (SPSS) software version 11.5. Intention-to-treat analysis was used by replacing the missing data with series mean for each group. Both descriptive and inferential statistics were determined. A bi-directional α-level of significance was set at *p*= 0.05 for all measures.   - Descriptive statisticsa was used for demographic results which are expressed as mean (± standard deviation; SD) and percentage unless otherwise indicated. - Chi-square tests were used for evaluating categorical variables. - Continuous variables between study and control groups were compared with unpaired *t-*tests. - Continuous variables between baseline and at the end of study for each group of patients were compared by using paired student *t-* tests. - Analysis of covariance (ANCOVA) was used for controlling covariate factors if baseline data are different between the patient groups. - One-way repeated analysis of variance (ANOVA) was used to examine the main effects of time when comparing data obtained at one time to data obtained at another time during the study period. - One-way repeated analysis of variance (ANOVA) with between-subjects factor was used to determine the main effects of overall difference between the control and the study groups with respect to the mean of the data. |
|  |
| ***13. Details of any clinical safety reporting processes and when applicable, specific risk management interventions to safeguard subjects*** |

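### One list covers both stopping the drug and leaving the study, so patients can be withdrawn for a fluid event and then given their group's average fluid value

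*Protocol*

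**What the plan says.** Protocol section 10 has one list, headed "Withdrawal or termination criteria", with three items:

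- Item 1: "The occurrence of heart failure or volume overload after drug administration which resulted in treatment needed or consent form withdrawal".
- Item 2: "The occurrence of side effect which resulted in consent form withdrawal such as dizziness that affect driving, diarrhea that affect routine life".
- Item 3: "The occurrence of severe infection, cardiac arrhythmia, myocardial infarction and cardiovascular hospitalization". This item carries no consent condition.

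The list says when a patient is withdrawn. It does not say whether that means coming off pioglitazone, leaving the study, or both.

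The same protocol makes fluid the subject of the comparison. Section 12 states: "The sample size was determined by using change in body fluid as the primary outcome measure". The second objective in section 3 begins: "To determine side effects related to weight gain and fluid retention and the incidence of edema of low-dose pioglitazone". Section 4 schedules visits every four weeks to week 24. For gaps in the data, section 12 states: "Intention-to-treat analysis was used by replacing the missing data with series mean for each group".

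**The concern.** Item 1 withdraws patients because of a severe form of the outcome being compared. If withdrawal ends follow-up, later body-water, weight and HbA1c values are missing for the patients who retained the most fluid. The protocol's rationale is that the lower dose causes less retention, so its own hypothesis predicts more of these losses in the standard-dose arm. The trial is also open label, so decisions to treat overload or to leave are made with the dose known.

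Filling the gap with the group mean then gives a patient withdrawn for overload the fluid value of a typical patient who was not. The arm with more fluid events looks closer to the other arm than it is, and the filled-in values carry no variability. A later analysis plan cannot recover values that were never collected, so this belongs in the protocol.

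**Working it through.** **Effect size behind the plan.** Section 12 gives 37 per group, 80% power and two-sided 0.05, with 1.96 and 0.84. The effect and SD are in a figure that is not available, so 37 cannot be reproduced directly. Solving the usual formula n = 2(1.96 + 0.84)²/d² for d gives d = √(2 × 2.80²/37) = 0.651. The plan then goes to 40 per group for 10% loss. Direct calculation gives 37/0.9 = 41.1 or 37 × 1.1 = 40.7, so 40 is close, and nothing here turns on that.

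**Assumptions, none from the documents.** Fluid change is normal with SD 1, mean 0 on low dose and 0.651 on standard dose. Every patient above a fixed limit c is withdrawn and nobody below it is. The missing value becomes the mean of the remaining patients in the same arm.

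**Formulas.** For an arm with mean μ, let z = c − μ and λ = φ(z)/Φ(z).

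- Share withdrawn: 1 − Φ(z).
- Mean of those remaining, and of the arm after filling: μ − λ.
- Variance after filling: Φ(z) × (1 − zλ − λ²).

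**Worked case, c = 1.5.**

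- Standard dose: z = 0.849, φ = 0.278, Φ = 0.802, λ = 0.347. Mean 0.651 − 0.347 = 0.304. Variance 0.802 × 0.585 = 0.469.
- Low dose: z = 1.5, φ = 0.130, Φ = 0.933, λ = 0.139. Mean −0.139. Variance 0.933 × 0.772 = 0.720.
- Difference: 0.304 + 0.139 = 0.443 instead of 0.651.
- Standard error relative to complete data: √((0.469 + 0.720)/2) = 0.77, about 23% too small.

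**Range.** Simulation with 40 per group and 20,000 repeats; the formulas agree to within rounding:

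| Limit (SD) | Withdrawn, low / standard | Estimated difference | Standard error too small by |
|---|---|---|---|
| 2.5 | 0.6% / 3.2% | 0.60 | 6% |
| 2.0 | 2.3% / 8.9% | 0.53 | 12.5% |
| 1.5 | 6.7% / 19.8% | 0.44 | 23% |
| 1.0 | 15.9% / 36.3% | 0.35 | 37% |

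Overall loss in the second row is (2.3 + 8.9)/2 = 5.6% and in the third (6.7 + 19.8)/2 = 13.25%. The plan's 10% allowance lies between them, but only if all loss were driven by fluid.

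**What continued follow-up does to the week-24 contrast.** Take d = 0.66 and c = 1.65. Means of those remaining are 0.369 (standard, 83.9% remaining) and −0.108 (low, 95.1% remaining).

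- Without follow-up: 0.369 + 0.108 = 0.477, about 0.48.
- With follow-up, if leavers' off-drug values fall to the low-dose mean of 0: 0.839 × 0.369 + 0.951 × 0.108 = 0.412, about 0.41.

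Under that assumption the week-24 difference is smaller with follow-up than without it.

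**The case against.** The strongest reply is that the list names triggers and says nothing about what follows. A reader might infer that the protocol tells sites to take no measurement at the event and to hold no later visits. It does not say so. Section 4 provides scheduled visits with an adverse-event interview and 24-hour contact, and the text under section 13 on safety reporting is not in the copy available. The end of follow-up is an inference from the heading and from the absence of any later assessment in the available text.

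Three further limits are fair:

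- A reader might take any fluid gain or side effect as ending participation. Item 1 requires that treatment was needed or consent was withdrawn, so mild edema does not trigger it. Item 2 covers only side effects that led to consent withdrawal, and some of those patients may not be recoverable whatever the protocol says. Item 3 does not depend on consent.
- A reader might conclude that the events are lost. The triggering event can still be counted as incidence. What is at risk is the later continuous values.
- A reader might expect continued visits to restore the full difference and the planned power. The 0.41 against 0.48 above shows that they need not, so no recovered power is claimed.

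The sharp cut-off is also a strong assumption. Section 10 excludes edematous states and severe heart disease, so actual rates may lie near the top row of the table.

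These points limit the size of the bias. They do not remove the problem that withdrawal is linked to the primary outcome, that the list leaves sites to decide whether visits continue, and that the stated filling rule assigns an average value to these patients.

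**Conclusion.** The point holds in this form. The protocol does not separate stopping the drug from leaving the study. One reason for withdrawal is a severe form of the primary outcome, and section 12 would replace the resulting gaps with the group's mean. The expected effect is a smaller dose difference and a standard error that is too small.

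The size is illustrative only, since the documents give no event rate. With a true standardised difference of about 0.65 and an assumed cut-off, the estimate is about 0.60 with 3% of the standard arm withdrawn and about 0.44 with 20% withdrawn. The direction rests on the standard dose retaining more fluid, which is the protocol's own premise. It also rests on withdrawal ending data collection, which is inferred. Nothing here judges the clinical triggers.

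**What to change.** Leave the three clinical triggers as the investigators set them, and add a data-collection rule:

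1. State that meeting a criterion concerns study drug and does not by itself end participation. Record withdrawal of consent to follow-up as a separate decision.
2. At the time of the event, record body water, weight, edema and the laboratory tests.
3. Continue the scheduled visits to week 24 unless the patient withdraws consent to follow-up.
4. Analyse the observed values by randomised group instead of filling them with the group mean.
5. Report the value at the event beside the week-24 comparison.

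The consent wording in items 1 and 2 should not be edited as part of this change, because that would alter the triggers themselves.

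The cost is protocol wording, a set of measurements at each event, and visits already in the schedule. No extra patients are needed. The real drawback is that week-24 values taken off drug, possibly after fluid treatment, enter the comparison and may attenuate it, which is the reason for step 5.

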**Low Dose Pioglitazone Proposal**

| 1. ***Study title:*** *Safety and Efficacy of Low Dose Pioglitazone Compared with Standard Dose Pioglitazone in Type 2 Diabetes with Chronic Kidney Disease: a Randomized Controlled Trial* |
| --- |
|  |
| ***2. The purpose and rationale for the study*** |
| Throughout the world, chronic kidney disease (CKD) is a growing health concern because of its increasing prevalence and incidence rates and dismal outcomes. Despite technical advances in dialysis and transplantation, the prognosis of kidney failure remains poor. The U.S. Renal Data System provides statistics on individuals with end-stage renal disease (ESRD), which include individuals with kidney failure who are receiving dialysis, as well as kidney transplant recipients at all stages of CKD. This U.S. registry reported more than 76,500 deaths in patients with ESRD in 2001, an annual mortality rate in excess of 20% ^1^. By 2010, there will be a projected 160,000 new dialysis-dependent patients/year, double the current rate ^2^. The average life span of a patient entering a long-term dialysis program is 20-25 years less than that of the normal age-sex-race-matched U.S. population over the age of 45 ^3^. Among many factors, including treatment characteristics and co-morbid conditions, protein and calorie malnutrition has been shown to be a major risk factor for increased mortality in the ESRD patient population.^4^  Type 2 diabetes mellitus (T2DM) is one of the most important health problems and its disease prevalence has been increasing steadily all over the world. Similarly, the rising incidence of the chronic kidney disease (CKD) creates major problems for both healthcare systems and economies in future years ^5^. T2DM is often associated with CKD, and for 30 to 50% of patients receiving dialysis therapy, diabetes is the primary cause of end stage renal disease (ESRD)^6,7^. Identification and diagnosis of CKD is important to optimize clinical management recommendations for this complex patient population.  Therapeutic options for patients with T2DM and CKD are limited because the reduced glomerular filtration rate (GFR) results in an accumulation of certain drugs potentially leading to adverse side effects ^8^. Currently, thiazolidinediones (TZDs), synthetic exogenous agonists of the nuclear peroxisome proliferator-activated receptor-gamma (PPARγ), increase insulin sensitivity and inhibit adipose tissue lipolysis as well as possess anti-inflammatory and other beneficial vascular effects ^9^. TZDs undergo hepatic metabolism and has been demonstrated to be effective without increasing the risk of hypoglycemic episodes among patients with CKD ^10^. The pharmacokinetic profile of TZDS, is similar among subjects with normal or impaired renal function, remaining unaffected even by hemodialysis ^11^. Therefore, dosing of TZDs is not a required adjustment among patients with CKD.  Unfortunately, fluid retention and edema have emerged as the most common and serious side effects of TZDs and have become the most frequent cause of discontinued therapy ^12,13^. The mechanism through which TZDs induces fluid retention results from an increase in tubular sodium and water reabsorption in the collecting tubule and an increase in vascular permeability growth factors ^14^. Currently, using pioglitazone 15 to 45 mg daily is recommended for patients with T2DM. Patients with CKD might constitute a high risk population of TZDs related to fluid retention. Reducing fluid retention with low dose medications is important among those with CKD to continue the beneficial effects to optimize glycemic treatment without affecting the renin-angiotensin-aldosterone system and natriuretic peptides^15,16^. |

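### Baseline kidney function enters the body-fluid comparison only if an undefined baseline difference triggers ANCOVA; it should always be in the model

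*Protocol*

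**What the plan says.** **Eligibility (section 10, inclusion criterion 2).** The entry criterion reads "HbA1c>8% at least 12 weeks and diagnosed CKD according to" the KDIGO 2012 definition. Neither list of criteria sets a CKD stage or an eGFR limit. Section 4, item 6, times body composition to just after dialysis, so dialysis patients appear to be in scope. The same item lists creatinine among the tests taken before the first treatment.

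**Allocation (section 10).** "Block randomization divides subjects into low dose group and standard dose group equally". The next sentence refers to subgroups, but none is defined and no stratification factor is named.

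**Rationale (section 2).** "Patients with CKD might constitute a high risk population of TZDs related to fluid retention".

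**Primary outcome and size (section 12).** "The sample size was determined by using change in body fluid as the primary outcome measure", and "The target sample size was 37 subjects per group that will provide 80% power to detect a significant effect". The test is two-sided at 0.05.

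**Analysis (section 12).** Continuous variables are compared between arms with an unpaired t-test. ANCOVA is reserved for the case where the groups turn out to differ at baseline. The section names no covariate and gives no criterion for such a difference.

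**The concern.** The eligible population can run from early CKD to dialysis, while the blocks balance only the number of patients per arm. If the severity of kidney disease affects the change in body fluid, two things follow.

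First, the arms may differ by chance in kidney function, and the unadjusted difference then carries part of that imbalance. The conditional ANCOVA is the plan's safeguard, but its trigger is undefined. If the trigger is a significance test at baseline, most moderate imbalances in a trial of this size will not reach it.

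Second, when the arms happen to be balanced, the rule makes no adjustment. The variance due to kidney function then stays in the t-test and widens its standard error. Adjusting for a prognostic covariate gains precision whether or not the arms differ, and a rule conditional on imbalance gives up that gain.

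**Working it through.** **1. Inputs from section 12.** Two-sided alpha 0.05 (z = 1.96), power 80% (z = 0.84), 37 per arm before loss and 40 per arm after it. The expected difference and SD were taken from another study ("extrapolating expected changes and standard deviation from data in the study of the effect of pioglitazone in T2DM patients"). The formula with their values is a figure that is not shown, so 37 cannot be rebuilt from its own inputs.

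**2. Effect implied by 37 per arm.** d = (1.96 + 0.84) × √(2/37) = 2.80 × 0.2325 = 0.651 SD. By the normal formula this gives 80% power at 37 per arm. By the t distribution it gives 78.9%, which is the baseline for step 6.

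**3. Chance imbalance.** Assumption: a share p = 1/3 of patients has advanced CKD. Treating the number in each arm as an independent binomial with n = 40:

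| Share with advanced CKD | P(arms differ by ≥15 points) | P(arms differ by ≥20 points) |
|---|---|---|
| 20% | 12% | 3.5% |
| 1/3 | 19% | 7.5% |
| 50% | 22% | 9.3% |

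**4. Would the plan's ANCOVA catch it?** Assumption: a baseline difference means p < 0.05. At p = 1/3 and 40 per arm, the probability of an imbalance of 15 points or more that is also not significant (chi-square without continuity correction) is 0.143. Then 0.143/0.191 = 75% of such imbalances would go unadjusted. Example: 16 of 40 against 10 of 40 is a 15-point gap with p = 0.15. On a continuous scale with 37 per arm, the difference must exceed 1.96 × √(2/37) = 0.46 SD before it triggers.

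**5. Shift in the estimate from a 15-point imbalance.** Assumption: advanced CKD shifts fluid change by δ = 0.5 to 1.0 residual SD. The total SD is √(1 + p(1−p)δ²), with p(1−p) = 0.222.

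- δ = 0.5: total SD = √1.056 = 1.027; shift = 0.15 × 0.5/1.027 = 0.073 SD; 0.073/0.651 = 11%.
- δ = 1.0: total SD = √1.222 = 1.106; shift = 0.15 × 1.0/1.106 = 0.136 SD; 0.136/0.651 = 21%.

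**6. Precision gained by always adjusting.** Variance share R² = p(1−p)δ²/(1 + p(1−p)δ²). The effective standardised effect is 0.651/√(1−R²). Power is by t-test with 37 per arm.

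| δ | R² | Power |
|---|---|---|
| none (unadjusted) | – | 78.9% |
| 0.5 | 0.053 | 81.0% |
| 0.8 | 0.125 | 84.0% |
| 1.0 | 0.182 | 86.3% |

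**7. Validity.** In 40,000 simulated trials with 37 per arm, the unadjusted t-test rejected a true null in 5.0%, 4.9% and 5.0% of runs for R² = 0, 0.2 and 0.3.

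**The case against.** The case against the point is substantial, and much of it stands.

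- **Unstratified blocks are valid.** The t-test already allows for chance imbalance, and step 7 confirms that alpha is kept. A reader might infer that the primary comparison is biased or invalid. It is not.
- **The plan does have an adjustment rule.** A reader might infer that kidney function is never adjusted for, or that an imbalance could not be separated from the dose effect. Neither is supported: the ANCOVA in section 12 could include kidney function, and such adjustment would separate the two. The weakness is that the rule is conditional, its trigger is undefined and its covariates are unnamed.
- **The rationale speaks of CKD as a class.** A reader might take section 2 to say that kidney function is the main prognostic factor. It says only that CKD patients might be at high risk, and every participant has CKD. That severity predicts fluid change within this population is an inference. It has some support: section 2 places the mechanism in the renal tubule, and fluid would be read after dialysis in some patients and not in others. The documents give no size for it.
- **A 15-point imbalance is not likely.** It is roughly a one-in-five event under the assumed share.
- **Covariates are often left to the SAP, which is not shown.** That would excuse silence. Here the protocol itself states the data-dependent rule.
- **Stratification is a preference.** No cut-point has a source in the documents, and the allocation text is too unclear to exclude some undefined subgrouping. If the numbers 0-19 describe a block of 20, an incomplete block could leave up to 10 patients' difference within a stratum. Stratification alone would also leave the variance in a t-test.

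**Conclusion.** The point holds as a low-cost improvement in efficiency and robustness. With eligibility across CKD stages, no named stratification factor and ANCOVA only on an undefined trigger, adjustment for kidney function is left to chance and to a later judgement. The documents show neither an inflated error rate nor a requirement to stratify.

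The prevalence and the strength of the kidney-function effect are both assumed, and the 0.65 SD is back-calculated. At the weak end of the range the gain is about two points of power; at the strong end it is about seven. If kidney function does not predict fluid change, the adjustment gains nothing and costs one or two degrees of freedom.

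**What to change.** In section 12, for the primary outcome, replace the conditional ANCOVA with a prespecified one. It should always include baseline kidney function: eGFR from the pre-treatment creatinine, with an indicator for dialysis. Patients on dialysis can be given one fixed eGFR value, so that the indicator carries their level. The model applies whether or not the arms differ at baseline, and it should be settled before outcomes are compared between arms. The unadjusted t-test can stay as a supporting analysis.

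Stratifying the block randomisation by kidney function is optional. If it is used, section 10 should name the factor and the block size, creatinine must be available before allocation, and the stratum must also be in the model.

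The cost is one or two model terms, with no new measurement, visit or patient.

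### Filling missing values with the arm's own mean and testing them as real data makes standard errors too small, so the two-sided 0.05 level does not hold; the rule also leaves withdrawal related to fluid gain uncorrected

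*Protocol*

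**What the plan says.** Section 12 of the protocol fixes the missing-data rule itself: "Intention-to-treat analysis was used by replacing the missing data with series mean for each group". The same section sets the outcome, "The sample size was determined by using change in body fluid as the primary outcome measure", and a single two-sided 5% level for all measures ("A bi-directional α-level of significance was set at" 0.05). For the between-arm comparison, "Continuous variables between study and control groups were compared with unpaired" t-tests; paired t-tests, ANCOVA and repeated-measures ANOVA are also listed. The section describes no variance correction, multiple imputation or sensitivity analysis.

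On numbers, "The target sample size was 37 subjects per group that will provide 80% power to detect a significant effect", then "the 10% loss follow up of the calculated number is considered", and finally "the quantity of subject per group is 40, total is 80".

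Section 10 lists as its first withdrawal or termination criterion: "The occurrence of heart failure or volume overload after drug administration which resulted in treatment needed or consent form withdrawal". Section 3 has the incidence of edema as an objective of its own, alongside weight gain and fluid retention.

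**The concern.** Intention-to-treat says who is analysed and in which arm. It does not license a particular way of inventing missing values. A value set to the mean of its own arm adds nothing to the sum of squares but adds one to the sample size. The standard deviation falls, the divisor rises, and the test behaves as though no one had been lost. Significance is then declared more often than the protocol says, even when the losses have nothing to do with the outcome.

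The second matter is who goes missing. The trial asks about fluid retention, and a patient who develops volume overload may be withdrawn for it. If no later fluid value exists, that patient receives the average change of those who stayed in the same arm. Fluid gain is then understated where overload occurred. If overload is commoner on 15 mg, the difference between doses is pulled towards zero.

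**Working it through.** **Inputs.** From Section 12: 40 per arm, 10% loss, two-sided 0.05, unpaired t-test. The difference and SD behind the 37 are in figures not shown, so 37 cannot be rebuilt. Solving n = 2(1.96 + 0.84)²/d² for n = 37 gives d² = 15.68/37 = 0.424, so the implied target is d ≈ 0.65 SD.

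**Loss allowance.** 37/0.9 = 41.1, which rounds up to 42; 37 × 1.1 = 40.7, which rounds up to 41. The stated 40 leaves room for 3 of 40 (7.5%). Both 3 and 4 missing per arm are therefore shown.

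**Case A: the analysed change itself is filled, missing at random.** Let n be the number per arm and k the number observed. The filled variance is (k−1)s²/(n−1), divided by n; the correct one is s²/k. Hence

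reported SE / correct SE = √[k(k−1) / (n(n−1))]

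and actual α = 2·P(T with 2k−2 df > t-critical with 2n−2 df × that ratio). With n = 40 the critical value is 1.991 (78 df).

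| Missing per arm | SE ratio | Actual type I error |
|---|---|---|
| 2 (5%) | 0.949 | 6.3% |
| 3 (7.5%) | √(37·36/1560) = 0.924 | 7.0% |
| 4 (10%) | √(36·35/1560) = 0.899 | 7.8% |
| 6 (15%) | 0.848 | 9.6% |
| 8 (20%) | √(32·31/1560) = 0.797 | 11.8% |
| 12 (30%) | 0.696 | 17.2% |

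For 4 missing: 1.991 × 0.899 = 1.789 on 70 df, which gives 7.8%. Simulation with 200,000 trials gave 7.7% at 4 missing and 11.8% at 8. Fractions other than the planned loss are assumptions. Section 10 gives 74 subjects, that is 37 per arm; with 4 of 37 missing the ratio is 0.890 and the error 8.1%.

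**Case B: the raw week-24 value is filled and change is then taken from the patient's own baseline.** The filled patient's change now varies with the baseline, so its deviation is not zero. Simulation with 40 per arm, missing at random and assumed baseline-to-week-24 correlations of 0.3 to 0.98 gives an SE ratio of about 0.95 and type I error of about 6% (5.4 to 6.3%) at 10% missing. At 20% missing, type I error is about 7.5% (roughly 7 to 8%).

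**Outcome-related withdrawal (assumed figures throughout).** If a fraction w of an arm is withdrawn with a change 2 SD above the completers, the arm's full mean exceeds the completers' mean by 2w. With 4/40 on 15 mg and 1/40 on 7.5 mg, the difference is understated by (0.100 − 0.025) × 2 = 0.15 SD. That is 0.15/0.65 = 23% of the implied target and leaves about 0.50 SD.

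A different model supports the direction. It takes normal outcomes, a true difference of 0.65 SD, and withdrawal of everyone above a common threshold. With a threshold of 1.75 SD, 4% and 14% are withdrawn and the estimate falls to 0.49 SD. Thresholds of 1.5 to 2.0 SD give 0.44 to 0.53 SD.

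**The case against.** The strongest reply has four parts.

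First, the size of the inflation depends on what is filled, and Section 12 says only that missing data are replaced. This stands: 7.8% is conditional on Case A, and Case B roughly halves the excess or better. In both cases the error exceeds 5% at the planned loss.

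Second, filling a change score with the arm's mean leaves each arm's mean exactly where a complete-case analysis would put it. This also stands. A reader might infer that the imputation creates the bias in the fluid comparison. It does not: the bias comes from withdrawal that depends on the outcome, and mean filling fails to correct it. Deleting the sentence alone would not recover it either.

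Third, a reader might infer that overload is the primary outcome and that patients withdrawn for it are hidden. The documents do not support this. The primary outcome is change in body fluid, a continuous measure; overload is a withdrawal criterion; edema incidence is a separate objective, and Section 12 provides chi-square tests for categorical variables. Filling a continuous value does not delete an event. The content of Section 13 on safety reporting is not in the copy at hand, so it cannot be said that such events go uncounted.

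Fourth, Section 10 does not say that measurement stops at withdrawal, and values taken earlier are kept. This is fair. The text shown does not provide for fluid measurement at or after withdrawal, but that is a gap to close and not proof of loss.

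**Conclusion.** The rule is wrong as written, and the protocol fixes it itself. At the planned loss the true two-sided type I error is about 7.0 to 7.8% if the analysed change is filled, and about 6% if the raw week-24 value is filled at 10% missing. At 20% missing it is about 11.8% or 7.5%. These figures assume approximately normal data missing at random.

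The withdrawal criterion adds a separate risk. Fluid gain is understated in any arm with overload withdrawals that lack a later value, and the difference shrinks if they are commoner on 15 mg. Neither the frequency nor the dose pattern is in the protocol, so 0.15 SD is an illustration. A reader might go further and say that the trial's signal would be erased; that same illustration leaves about three quarters of the implied 0.65 SD.

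The two faults can push in opposite directions, but there is no reason for them to cancel.

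**What to change.** - Delete the series-mean sentence in Section 12. Define intention-to-treat as all randomised patients, analysed as allocated.
- Analyse change in body fluid with a mixed model for repeated measures (arm, visit, arm by visit, baseline value) on all observed visits, without single imputation. Multiple imputation would also serve. The four-weekly visit list in Section 4 does not name bioimpedance, so state at which visits fluid is measured; the model gains only from visits that have a value.
- Without changing the drug-stopping rule, separate stopping drug from leaving the study. Keep fluid measurements taken up to and at withdrawal, and later ones, including week 24, where consent remains.
- Count every heart-failure or volume-overload withdrawal as an event in the edema and fluid-retention comparison.
- Add a sensitivity analysis that gives those withdrawals unfavourable fluid values, because the mixed model recovers only what earlier visits predict.

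The cost is a rewritten analysis paragraph, continued measurement of a few patients, slightly wider intervals and one further analysis.
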